##### Data entry and data management

In the GLMC trial, all data will be electronically processed. Original study forms will be entered and kept on file at the participating site. Participant files are to be stored in numerical order and stored in a secure and accessible place. Participant files will be maintained in storage for a period of 10 years after completion of the study.

Additional errors will be detected by programs designed to detect missing data or specific errors in the data. The Data Manager will respond by checking the original forms for inconsistency, checking other sources to determine the correction, modifying the original (paper) form entering a response to the query.

##### Effectiveness analysis

Baseline similarity of the intervention and control groups will be assessed at cluster level (i.e.*,* communities of communes) and child level using descriptive statistics and *T*-tests or Mann-Whitney tests for continuous variables and χ^2^ or Fisher’s exact tests for categorical variables.

Linear mixed models will be used to determine the impact of the intervention impact; this will allow us to calculate fixed effects, such as the effect of randomization group, and random effects such as the effect of subjects and clusters given the potential for intraclass correlations (between and within subjects and clusters). Longitudinal analysis of the dichotomous primary endpoint (i.e.*,* achieving or not achieving the current internationally recommended PA level of 60 min of moderate to vigorous PA per day) will be conducted with a logit link function, effects of subject, group, time and cluster and the time*group interaction will be calculated. The effect of the intervention will be evaluated at child (and parent) level, but also at school, commune and community of communes levels. Potential confounders such as age and sex will be included in the model as covariates.

The same analytical approach will be applied to the secondary outcome variables. The effect of the intervention on TPB variables and other psychosocial continuous variables will be assessed using similar linear mixed models, with a regress link function.

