### Study design and population

All the year 3 and year 4 children attending primary schools in the Hérault, Gard, and Aude departments of France (and their parents) are eligible to participate in the study. There is wide variation in the sociodemographic background and PA levels of children attending schools in these departments. The intervention involves children and their parents, and is implemented by multiple local, grass-roots partners, namely, school teachers, municipal officials and policy stakeholders from community agencies and district councils. To avoid contamination between the intervention and control groups randomization will be done at community of communes level (a community of communes is an administrative grouping of several cities or villages), thus all the schools in a given community of communes will represent a cluster.

The study is a two-armed prospective cluster-randomized, controlled intervention trial. Communities of communes will be randomized in equal proportions to one of the two study arms: 1) the GLMC experimental arm, which will receive a 24-month (6 weeks per year) multilevel, extended TPB-based program intended to promote PA; 2) the control arm, which will not receive any intervention (Fig. 1).

After randomization, schools belonging to the communities of communes and their teachers will be informed about the study and their arm allocation by a research assistant. A member of staff outside the research team will introduce data into the computer in separate datasheets so that the researchers can analyze data without having access to information about the allocation. Eligible children from schools and classes willing to participate in the study, and their parents, will receive a written note explaining the research goal, design, assessment protocol (including information about the wearing of accelerometers) and intervention content (see flow diagram of schedule in Fig. 2). Children with medical conditions or and children taking medication that would limit their physical activity will not be included. Children will be given consent forms to take home for their parents to sign. There are three independent consent forms providing: *(i)* consent to the child filling in questionnaires; *(ii)* consent to fill in the parental questionnaires; *(iii)* consent to the child wearing an accelerometer.

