### Statistical considerations

#### Power analysis

Without considering the clustering effect, it is calculated that 180 children per randomization group are needed to observe a 15% difference in the proportions of children in the intervention and control groups achieving the current internationally recommended level of PA with 80% power, given a two-tailed type I error rate of 5%. We assumed that 35% of children would be achieving the current internationally recommended PA level of 60 min of moderate to vigorous PA per day at baseline.

The clustering structure of the randomization requires a variation inflation factor equal to *1 + (m(1 + cv*^*2*^*)-1)r* [58] where *m* is the mean number of children per cluster; *cv* is a coefficient of variation equal to ratio of the standard deviation of the cluster sizes and *m*; *r* is the intraclass correlation coefficient (ICC) for the communes of one community of communes (i.e.*,* one cluster) and reflects the degree of cluster homogeneity. *r* was set at 0.005 based on preliminary data obtained from pilot studies and the database of ICCs [56] .

Given the number of children in selected community of communes clusters (*m* = 781 children on average; *cv* = 1.05), 3400 subjects are required to observe a 15% difference in the proportion of each group reaching the current international recommendation of 60 min with 80% power. Assuming a loss-to-follow-up rate of 15%, a reasonable estimate of the required sample size is 4000 subjects, i.e.*,* 2000 in the intervention group and 2000 in the control group, corresponding to around 160 classes.

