#### Statistical analysis

Data will be analyzed on an intention-to-treat basis using Stata software (version 13, StataCorp, College Station, USA). All the statistical tests will be two-sided and *p*s < 0.05 will be considered significant. The number of included subjects and the enrolment curve, the number of theoretical follow-ups corresponding to the number of included subjects, the number of follow-ups actually carried out and the relation between the two will be presented by the randomization group. The cumulated follow-up duration will be calculated and the actual cumulated follow-up duration expected will be presented. The data analysis, carried out on intention to treat will include: (a) the comparison of the enrolment groups (for both the children and the children characteristics), (b) the analyses described below, (c) the missing data sensitivity analysis to determine the statistical nature of the longitudinal data (Missing At Random or Not Missing At Random).

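### Child-level baseline tests ignore the cluster randomization; for a balanced variable with an ICC near the planning value of 0.005 they would reject roughly 40–50% of the time instead of 5%

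*Protocol article*

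**What the plan says.** The Study design and population section of the protocol article sets the unit of randomization: "Communities of communes will be randomized in equal proportions to one of the two study arms". The Power analysis section treats clustering as something that must be allowed for. It gives an inflation factor with a mean of 781 children per cluster and a coefficient of variation of cluster size of 1.05, and the intraclass correlation "was set at 0.005 based on preliminary data obtained from pilot studies" and a published database.

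The Effectiveness analysis section then says "Baseline similarity of the intervention and control groups will be assessed at cluster level" and, in the same sentence, at "child level using descriptive statistics and *T*-tests or Mann-Whitney tests for continuous variables", with χ² "or Fisher’s exact tests for categorical variables". No allowance for clustering is attached to the child-level tests. The next paragraph of that section does put random cluster effects into the effectiveness models. The Statistical analysis section applies one threshold throughout and does not exempt the baseline tests: "All the statistical tests will be two-sided and *p*s < 0.05 will be considered significant".

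On timing, the Study design and population section says: "After randomization, schools belonging to the communities of communes and their teachers will be informed about the study and their arm allocation". It then describes eligible children from willing schools and classes receiving the study information and the consent forms.

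**The concern.** In their standard form, all four named tests assume that children are independent observations. Children in one community share an arm and some of their characteristics, so the true variance of a between-arm difference exceeds what these tests use, and the p-values come out too small. The protocol accepts this for its sample size and its effectiveness models but not for its baseline comparison.

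This matters because schools and teachers know their arm before children are invited and parents consent. In the second pilot study only 16 of 53 contacted schools (30%) agreed to take part, so there is room for participation to differ by arm. A baseline comparison is one of the places where a reader looks for that. If the test often rejects with no selective recruitment at all, a significant result there says little.

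**Working it through.** **Inputs.** From Power analysis: 180 children per arm before clustering, m = 781, cv = 1.05, r = 0.005, 3400 children before and 4000 after 15% loss, 35% meeting the guideline at baseline. From Statistical analysis: two-sided 5%. From Feasibility studies: 30% of schools agreed, and consent for the child's participation was returned for 86.7%.

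**Step 1: reproduce the plan's own figures.**
- 35% v 50%, 80% power, two-sided 5%: 170 per arm, or 183 with continuity correction (stated: 180).
- Inflation factor: 1 + (781 × (1 + 1.05²) − 1) × 0.005 = 1 + (781 × 2.1025 − 1) × 0.005 = 9.205.
- 2 × 180 × 9.205 = 3314, and 2 × 183 × 9.205 = 3369 (stated: 3400, within 3% of both).
- 3400 / 0.85 = 4000, as stated.

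So a factor of about 9.2 is what the plan used.

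**Step 2: effect on an unadjusted test.** If the true variance is VIF times the assumed variance, a nominal 5% two-sided test rejects a true null with probability 2 × (1 − Φ(1.96 / √VIF)).
- VIF = 9.205: 1.96 / 3.034 = 0.646, giving 51.8%.
- VIF = 3400 / 360 = 9.44, the factor implied by the stated total: 52.4%.

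**Step 3: check by simulation.** Step 2 is a large-sample formula, and the article's text gives no number of communities. A simulation used 4000 children in total, beta-binomial clusters with 35% prevalence and ICC 0.005, gamma-distributed cluster sizes with cv 1.05, half the clusters per arm, and an unadjusted two-proportion test (20,000 runs per setting). It gave 42% with 4 clusters and 39% with 6. With the total held at 4000, more clusters means smaller ones and a lower rate: 33% with 10 and 24% with 20.

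**Step 4: the other reading of 781.** The article does not make clear whether 781 counts enrolled or eligible children. If it counts eligible children, and the pilot rates carry over (both assumptions), the enrolled mean is 781 × 0.30 × 0.867 = 203. Then VIF = 1 + (203 × 2.1025 − 1) × 0.005 = 3.13, and the rate is about 27%.

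**Step 5: dependence on the ICC.** The value 0.005 is given only in the power calculation for the physical activity endpoint. With m = 781 and cv = 1.05:

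| ICC | VIF | Actual rejection rate |
|---|---|---|
| 0 | 1.00 | 5% |
| 0.0005 | 1.82 | 15% |
| 0.002 | 4.28 | 34% |
| 0.005 | 9.21 | 52% |
| 0.02 | 33.82 | 74% |

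**The case against.** Several points count against the concern, and most of them limit it.

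- **The same sentence also plans a cluster-level comparison and descriptive statistics.** This stands. At cluster level the community is the unit, so the inflation does not arise. It does not correct the child-level p-values, though, and the article does not say which level prevails if they disagree.
- **The effectiveness models carry random cluster effects.** This stands. The harm is confined to reading the baseline comparison.
- **The planning ICC belongs to one endpoint.** This stands. No ICC is given for age, sex or the psychosocial scores, so no single rejection rate applies to all baseline variables. Stratification by department and residential environment could also lower the rate for variables related to those factors.
- **The baseline table is not the only evidence on recruitment.** This stands too: the Statistical analysis section also reports inclusions and the enrolment curve by group.

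A reader might go further in two directions that the document does not support. One is to divide 4000 by 781, conclude that there are about 5 communities, and say that the cluster-level tests can never reach p < 0.05. The text states no number of communities and the figures are not shown. Three departments by two environments make six strata, which 5 communities could not fill, and on the other reading of 781 there would be about 4000 / 203 ≈ 20. Even with 2 v 3 communities, the listed t-test on cluster means can reach p < 0.05.

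The other is that false alarms will decide which covariates enter the primary model. Age and sex are named in advance as examples of confounders, and nothing ties covariate choice to baseline p-values.

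**Conclusion.** The point holds in a limited form. The child-level baseline tests, as named, treat children as independent and conflict with the protocol's own allowance for clustering. For a balanced variable with an ICC near 0.005, a nominal 5% test would reject roughly 40–50% of the time: 52% by the large-sample formula and about 40% by simulation with 4 to 6 clusters. The figure falls to about 27% if 781 counts eligible children and the pilot rates apply. Outside that ICC the rate ranges widely, and only an ICC of essentially zero gives the nominal 5%. It would be too strong to say that half of all balanced baseline variables will be flagged.

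The primary effect estimate and its test are not affected. What is lost is the use of the child-level p-values as a check on selective recruitment, in a trial where allocation is known before children are invited. The change is worth making before the baseline data are analysed.

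**What to change.** In the Effectiveness analysis section, remove the unadjusted child-level significance tests. Describe baseline variables by arm, for example with standardised differences and the spread of community-level means. If child-level tests are kept, replace them with a mixed model (linear or logistic, to suit the variable) that has a community-of-communes random effect, in line with the effectiveness models in the same section.

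This is a change of wording. It needs no additional data and does not alter the sample size or the primary analysis.

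### The arm effect is to be tested at p < 0.05 with a logit mixed model and no small-sample inference is named, although communities are randomized and the plan's figures imply few of them

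*Protocol article*

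**What the plan says.** Under Study design and population, and Randomization, the protocol article randomizes communities of communes in equal proportions, stratified by department (three) and urban or rural environment (two).

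Under Effectiveness analysis it says "Linear mixed models will be used to determine the impact of the intervention impact", with random effects for subjects and clusters. The dichotomous primary endpoint gets a logit link with subject, group, time, cluster and time-by-group effects, and the secondary outcomes follow the same approach. Under Statistical analysis, "All the statistical tests will be two-sided" at p < 0.05, in Stata 13.

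Power analysis sizes the trial for 80% power at a two-sided 5% level. It takes a 35% baseline proportion, a 15% difference, an intraclass correlation of 0.005, a cluster-size coefficient of variation of 1.05, and communities of "781 children on average". It arrives at 3400 children, or 4000 after 15% loss.

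The article names no reference distribution, degrees-of-freedom method, choice between maximum and restricted likelihood, or number of communities.

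**The concern.** Arm is assigned to whole communities, so the information about a between-arm contrast is limited by how many communities there are, however many children each contributes. Likelihood-based mixed-logit output ordinarily refers a fixed effect to the normal distribution. With few communities that reference is too narrow, and a maximum-likelihood estimate of the between-community variance also tends to be too small. Both errors act in the same direction, and both can occur with the community effect properly in the model.

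At stake are the error rate of the primary test and of every secondary arm comparison, the width of their intervals, and the stated 80% power, which was computed from normal quantiles.

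**Working it through.** **1. The plan's sample size reproduces.**
- 35% against 50%, two-sided 5%, 80% power: 170 per arm, or 183 with continuity correction. The plan states 180.
- Design effect: 1 + (781 × (1 + 1.05²) − 1) × 0.005 = 9.205.
- 2 × 180 × 9.205 = 3314 and 2 × 183 × 9.205 = 3369. The plan states 3400.
- 3400 / 0.85 = 4000, as stated.

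**2. Most of the variance lies between communities.** The between-community share of the variance of an arm mean is (9.205 − 0.995) / 9.205 = 89%.

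**3. Number of communities, K.**
- If 781 is enrolled children per community: 3400 / 781 = 4.4 and 4000 / 781 = 5.1, so about 5.
- If 781 is eligible children and the rates under Feasibility studies apply (30% of schools, 86.7% child consent; an assumption): 781 × 0.30 × 0.867 = 203 per community. Then 3400 / 203 = 16.7 and 4000 / 203 = 19.7, so about 17 to 20.

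**4. Type I error of a nominal 5% normal-reference test.** The contrast is taken to vary between communities.
- (a) Unbiased variance, similar communities: P(|t on K − 2 df| > 1.96).
- (b) Maximum-likelihood variance, similar communities: P(|t on K − 2 df| > 1.96 × √((K − 2)/K)).
- (c), (d) Simulation, 20,000 runs per setting, of a correctly specified random-community logit model at one time point. It used a normal likelihood on community logits, 3400 children, intraclass correlation 0.005 and coefficient of variation 1.05.

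| K | (a) | (b) | (c) simulated, restricted likelihood | (d) simulated, maximum likelihood |
|---|---|---|---|---|
| 5 | 14.5% | 22.6% | 14.9% | 23.5% |
| 10 | 8.6% | 11.8% | 9.6% | 14.6% |
| 20 | 6.6% | 7.9% | 7.6% | 9.5% |
| 40 | 5.7% | 6.4% | 6.4% | 7.1% |

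**5. Same simulation with a t reference on K − 2 df.** K = 5: 4.4% (restricted likelihood) or 8.0% (maximum likelihood). K = 20: 5.9% or 7.5%. The t reference with restricted likelihood is close to nominal. With maximum likelihood an excess remains.

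**6. Power with the t reference.** This is the noncentral t with noncentrality 1.96 + 0.84 = 2.80, the value that gives 80% under normal quantiles.

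| K | critical value | interval width relative to 1.96 | power |
|---|---|---|---|
| 5 | 3.18 | 1.62 | 48% |
| 6 | 2.78 | 1.42 | 56% |
| 10 | 2.31 | 1.18 | 69% |
| 20 | 2.10 | 1.07 | 75.5% |

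**7. Limits on the remedy when K is small.**
- Department and residence as main effects use 2 + 1 = 3 df. At K = 5 this leaves 5 − 2 − 3 = 0. At K = 20 it leaves 15.
- With 6 communities split 3:3 there are 20 allocations even without strata, so the smallest two-sided permutation p-value is 2/20 = 0.10.

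**The case against.** **The article never says that large-sample p-values will be used.** This stands. A reader might infer that the plan commits to a normal-reference test. The text is silent, a mixed model with a community effect is compatible with restricted likelihood and between-community degrees of freedom, and an analysis plan that is not shown may specify them. What remains is that the article fixes a model family and a threshold whose ordinary output is unreliable at the cluster counts its own figures imply. For the binary primary endpoint the remedy also goes beyond a software option.

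**The excess does not occur in every correctly specified model.** This also stands. A reader might infer that it persists whatever the random effects. The plan includes a time-by-group interaction and a baseline measurement. If change over time did not vary between communities, that interaction would be essentially a within-child contrast and a normal reference would be close to nominal. The calculations above describe a single-time comparison. Zero community-by-time variance is nevertheless unlikely: the protocol leaves the physical activity events to local policy stakeholders, and weekend events are organised separately in each community.

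**The number of communities is unknown.** Five would not fill the six department-by-residence strata, which makes the low count doubtful, and 781 may count eligible children. At about 20 communities the excess is modest. It is still above 5%, and nothing in the article guarantees 20.

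**Conclusion.** The concern holds conditionally. If the arm effect is judged by the ordinary asymptotic test, and the intervention contrast varies between communities, the true error at nominal 5% is roughly 15 to 23% with 5 communities and roughly 7 to 9% with 20. The higher figure in each pair comes from maximum-likelihood variance and, at 20 communities, from the unequal community sizes that the plan itself states. Both cluster counts are inferred, and the higher one rests on applying the pilot take-up. The sample-size arithmetic is not in dispute. The weakness is that it uses normal quantiles and so takes no account of the few degrees of freedom behind the arm comparison.

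**What to change.** 1. State the number of communities, in total and per arm, and say whether 781 counts enrolled or eligible children.
2. Judge the arm effect (time by group) against a t distribution with between-community degrees of freedom. Use restricted-likelihood mixed models for continuous outcomes and, for the primary endpoint, a baseline-adjusted community-level analysis of the T3 proportions.
3. Keep stratum terms few enough to leave usable degrees of freedom.
4. Add a permutation test that re-randomizes communities within the strata only if there are enough communities for p < 0.05 to be attainable.
5. Restate power on the same basis.

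The analysis change is wording and code, but it is not free. Against a 1.96 multiplier, intervals widen by about 7% with 20 communities and about 62% with 5. The planned 80% power becomes about 75.5% and about 48% respectively, before any loss to stratum terms. If the count is near the low end, no choice of test restores the stated power with that number of communities.

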### Evaluation

All variables will be measured at four time points (Fig. 1) i.e.*,* pre- and post-intervention in each year of the two-year intervention:year 1: pre-intervention 1 (T0); baseline;year 1: post-intervention 1 (T1); at the end of intervention 1, 4.5 months after baseline;year 2: pre-intervention 2 (T2);12 months after baseline, 7.5 months after the end of intervention 1;year 2: post-intervention 2 (T3); end of intervention 2, 16.5 months after baseline.

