##### Analysis of the mediating effect of psychosocial variables

Mediation analyses are an important step in evaluation of theory-based interventions as they help to determine the extent to which behavioral change during the intervention is explained by changes in the variables included in the underlying theoretical model [24]. To test whether the effect of the GLMC on children’s PA levels is mediated by the variables specified in the underlying theoretical model (Fig. 3) we will perform sequential mediation analyses using the SPSS (version 21) macro PROCESS, with 10,000 bootstrapped replications [59]. PROCESS allows one to conduct multiple mediator analysis in linear multiple regression models whilst accounting for covariates (e.g.*,* age, sex, PA level at T0). The independent variable of the model will be the group, (coded 1 for the intervention group and 0 for the control group). The dependent variable will be PA level at T3. The multiple mediation analyses will include 3 sequences of mediators (see [60, 61] for a similar approach). Change in parental shared family PA and parental social support for PA between T0 and T3 will constitute the first sequence of mediators, change in children’s attitudes, subjective norms and perceived behavioral control between T0 and T3 will constitute the second sequence of mediators, and change in children’s intentions, perception of activity opportunities and planning between T0 and T3 will constitute the third sequence of mediators. In addition, moderation analyses will be conducted to test whether the effects of change in intentions on the level of PA of children is moderated by different levels of perceptions of activity opportunities and different levels of planning (see Fig. 3). The results of analyses will be presented using two types of coefficients: a regression coefficient (*β*) for each parameter and an indirect effect coefficient (*θ*) for each indirect pathway (via a specific mediator) between the independent variable (group) and the dependent variable (PA at T3). All the statistical tests will be two-sided and *p*s < 0.05 will be considered significant.

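### The primary model, as it naturally reads, treats T0 activity as one more outcome wave, so the T3 effect becomes a difference in change from T0; using T0 as a true baseline would be more efficient in large samples

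*Protocol article*

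**What the plan says.** Under Study objectives, the primary aim is the effect on the proportion of children meeting the 60-minute recommendation at T3. Under Evaluation, "All variables will be measured at four time points", T0 to T3, with T0 labelled as baseline.

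Under Effectiveness analysis, the dichotomous primary endpoint goes into a longitudinal mixed model with a logit link, where "effects of subject, group, time and cluster and the time*group interaction will be calculated". The random part is described as "random effects such as the effect of subjects and clusters given the potential for intraclass correlations". On adjustment, "Potential confounders such as age and sex will be included in the model as covariates". T0 activity is not named there. The same approach is to be applied to the secondary outcomes.

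T0 activity is named as a covariate only in the mediation analysis of activity at T3, which is described as "accounting for covariates (e.g.*,* age, sex, PA level at T0".

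Under Power analysis, the starting point is that "180 children per randomization group are needed to observe a 15% difference in the proportions of children in the intervention and control groups", at 80% power and a two-sided 5% level. This is inflated for clustering to 3400 and for 15% loss to 4000. No T0–T3 correlation enters the calculation, and none is given anywhere in the article.

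**The concern.** Randomization makes the arms equal in expectation at T0. A model with free group, time and time-by-group terms does not use that fact. It estimates a separate group difference at T0 and then measures the T3 effect relative to it. There are two consequences.

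- **Precision.** Subtracting a noisy baseline contrast costs more variance than regressing on it. Reading the T3 group contrast directly from the same free-group model does not help, because T0 then provides essentially no adjustment.
- **Chance imbalance.** Suppose the arms differ by d at T0 by chance. With no treatment effect, the expected T3 difference is R·d. The change contrast subtracts the whole of d and leaves −(1−R)·d in the estimated effect. At R = 0.5 that is half the imbalance. When whole communities are randomized, such imbalance is more likely than with individual allocation.

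The planned sample size is for a comparison at one time point, so its 80% belongs neither to a change contrast nor to a baseline-adjusted comparison.

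**Working it through.** **1. The plan's own figure.** Inputs from Power analysis: 35% against 50%, two-sided 5%, 80% power, mean cluster size m = 781, cv = 1.05, ICC 0.005.
- Two proportions at one time: 170 per arm without continuity correction and 183 with it. The article states 180.
- Inflation factor: 1 + (781 × (1 + 1.05²) − 1) × 0.005 = 9.205.
- Clustered total: 2 × 180 × 9.205 = 3314, or 2 × 183 × 9.205 = 3369. The article states 3400.
- 3400 / 0.85 = 4000.

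The figure reproduces to within about 3%, as a T3-only comparison that makes no use of baseline.

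**2. Relative variance of the T3 effect.** Let R be the T0–T3 correlation of the arm contrast, with equal variances at both times.
- T3 alone: 1
- Change from T0: 2(1 − R)
- T0 used as baseline: 1 − R²
- Ratio of the last two: (1 − R²) / (2(1 − R)) = (1 + R)/2, which is below 1 for every R < 1.

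**3. Power if T3 alone has 80%.** Power = Φ(2.802/√v − 1.960), where v is the relative variance. R is an assumption throughout.

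| R | Change contrast | T0 as baseline | Variance ratio |
|---|---|---|---|
| 0.3 | 66% | 84% | 0.65 |
| 0.4 | 72% | 86% | 0.70 |
| 0.5 | 80% | 90% | 0.75 |
| 0.6 | 88% | 94% | 0.80 |
| 0.7 | 95% | 98% | 0.85 |

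The change contrast has less power than T3 alone when 2(1 − R) > 1, that is, when R < 0.5.

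**4. What R means in this design.** The between-community share of the variance of a community mean is 0.005 / (0.005 + 0.995/781) = 0.80. It is 0.89 if m(1 + cv²) replaces m. R is therefore mainly the stability of community means over time. With community autocorrelation C and child-level correlation ρ,

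R = (0.005·C + 0.995·ρ/781) / (0.005 + 0.995/781).

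For ρ = 0.4, R is 0.40 at C = 0.4, 0.48 at C = 0.5, 0.56 at C = 0.6 and 0.72 at C = 0.8. If the community effect is constant over time (C = 1), R is about 0.84 to 0.96 for ρ from 0.2 to 0.6 across both cluster sizes.

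**5. Few communities.** The table assumes many clusters. Taken literally, 4000/781 is about 5 communities, although the article does not state the number and 781 may count eligible rather than enrolled children. Simulated t-tests on equally weighted community means at R = 0.5, with the effect set to give 80% normal-theory power for T3 alone, gave the following power for change against adjustment for the community's T0 mean:
- 5 communities: 48% against 34%
- 6 communities: 57% against 50%
- 8 communities: 64% against 67%
- 10 communities: 70% against 74%

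A community-mean covariate loses power at 5–6 communities and gains only a few points at 8–10.

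All figures are linear approximations on the risk-difference scale.

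**The case against.** The article does not say outright that T0 is an outcome row, or which coefficient is the primary test. Its covariate list is open-ended, and a condensed article may leave the parameterisation to the analysis plan. That stands as a caution: the point rests on the natural reading. But the article does commit to specific model terms, and under those terms T0 has no other role.

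A reader might infer that the trial is underpowered. The documents do not support that. A shortfall needs R below about 0.5, chiefly at community level, and no such figure is given. A child's unreliable 7-day recall does not settle it, because most of the variance of the contrast lies between communities. The random effects named are for subjects and clusters, with no cluster-by-time term. If that structure were true, R would be high and the change contrast would exceed 80%. Equally, nothing in the article shows that communities are that stable.

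A reader might also infer that keeping T0 on the outcome side is an error in itself. It is not. With a common T0 mean across arms, such a model has about the efficiency of covariate adjustment, and it keeps children with missing waves. Nor does the mediation analysis contradict the primary one: it models T3 alone, so T0 can only enter as a covariate. It shows only that T0 activity is available and considered relevant.

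**Conclusion.** The point holds as one of efficiency and robustness to baseline imbalance, not as a demonstrated loss of power. On the natural reading of Effectiveness analysis, the T3 effect is a difference in change from T0. In large samples this needs 2/(1+R) times the sample size of an analysis that uses T0 as a baseline: 1.54 times at R = 0.3, 1.33 at 0.5 and 1.18 at 0.7. The direction does not depend on R. The size does, and R must be assumed. With very stable communities the power gain is negligible, since both analyses are then close to full power: about 95% against 98% already at R = 0.7. Whether the change contrast would fall short of 80% is neither stated nor ruled out by the documents. With few communities, the large-sample gain cannot be assumed for an adjustment that uses up a cluster-level degree of freedom.

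**What to change.** In Effectiveness analysis, name the T3 group difference as the primary effect and state how T0 enters, by one of two routes:
- keep T0 to T3 as outcomes in the longitudinal logit mixed model, but constrain the arms to a common mean at T0, which retains children with missing waves; or
- enter the child's T0 activity as a covariate, with T1 to T3 as outcomes.

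Do the same for each secondary outcome, using its own T0 value. Add a community-mean T0 covariate only if the number of communities can bear the lost degree of freedom; with about 5–6 it would reduce power. If power is claimed for the chosen model, state the T0–T3 correlation assumed, at child and community level.

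The cost is a sentence or two of wording and no new data. The covariate route also needs a rule for children without a T0 value, so that they stay in the intention-to-treat analysis.
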